## Methods and Design

### Protocol Outline

This study was designed as a prospective observational study. It will be conducted in Moscow, Russia (Department of Neurology, I.M. Sechenov First Moscow State Medical University).

In-patients aged 60–75 diagnosed with cSVD according to current diagnostic criteria and neuroimaging standards (51, 54) will be evaluated for MRI markers of cSVD and cognitive function over a period of 2 years. General assessment of risk factors for cardiovascular disease will include identification of hypertension (office measured off medication conventional blood pressure of at least 140/90 mmHg), measuring total cholesterol level, calculation of body mass index, as well as revealing by self-report and exploring the medical history the presence of ischemic heart disease, diabetes, and heart rhythm disturbances. Additionally, the duration of smoking and habitual alcohol consumption will be assessed. For the latter purpose, a validated Russian version of the Alcohol Use Disorders Identification Test (AUDIT) will be applied (58).

The design of the study is schematically depicted in Figure 1. All enrolled patients will undergo overnight PSG at baseline. Based on PLMI, all patients will be divided into the experimental (PLMI ≥15/h) and control groups (PLMI <15/h). The assessment of the night sleep and quality of daytime functioning will be made at baseline only. Assessment of cognitive function and brain MRI will take place at weeks 0 (baseline) and 104 (2-year follow-up). The details on the applied study techniques and evaluation of night sleep, cognitive function, and MRI are given in parts 2.4, 2.5, and 2.6, respectively. The examination protocol is resumed in Table 1.

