The patients responding to the criteria of inclusion without conditions listed in part 2.2.2 will undergo the routine general clinical assessment and study procedures (nocturnal PSG, neuropsychological assessment, and brain MRI). Patients with identified apnea/hypopnea index (AHI) equal to or more than 5 will be excluded, as well as subjects with conditions mentioned in part 2.2.3. All enrolled patients will be given recommendation according to 2019 American College of Cardiology/American Heart Association Guideline on the Primary Prevention of Cardiovascular Disease (65) for the purpose to manage generally recognized risk factors for cardiovascular disease.

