Since the progression of cSVD features depending on PLMI is the key point of our study and linear regression will be applied, we calculated the sample size (N) based on this type of design. As mentioned above, there are seven independent variables (*p* = 7): age, arterial hypertension level, body mass index, blood sugar level, ischemic heart disease, cholesterol level, and smoking duration, and one tested parameter (PLMI or other parameters of PLMS). The sample size should be calculated depending on effect size: N = 392 + p for small, N = 52 + p for medium, and N = 22 + p for large effect size respectively (104). Thus, for revealing medium effect size, N = 52 + 7 = 59 participants should be enrolled, and for revealing small effect size, N = 392 + p, or 392 + 7 = 399 participants should be enrolled. A large effect size of PLMS is not expected. Therefore, 59 patients should be enrolled initially, and when no effect is revealed, the sample size should be enlarged up to 399. On the other hand, a comparison of cSVD feature prevalence between two groups is also planned as interim analysis. For this purpose, unpaired *t*-test (or Mann–Whitney test, depending on whether the distribution is normal) will be applied, and it requires standard deviation (SD) to calculate the sample size. When SD = 1.22 [obtained by Kang et al. (51)] and given probability for rejecting the null hypothesis α = 0.05, probability of failing to reject the null hypothesis under the alternative hypothesis β = 0.2 and effect size = 0.5, group size *N* = 49 is received when rounded up to the next highest integer. Therefore, at least 49^*^2 = 98 patients should be enrolled, but this number could be changed after another value of SD will be received.

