The reported association between high PLMI and transient sympathetic increase does not clarify whether it is a cause-and-effect connection or these events have the same origin. In this regard, more research using controlled trials is needed to demonstrate the positive impact of prolonged treatment of PLMS on cardiovascular health. The absence of a treated group is also one of the limitations of our study. It could establish the utility of pharmacological reduction PLMS.

Another significant limitation of the proposed study design should be discussed. The baseline level of both cognitive function and WMH volume determinates the speed of further progression of the cSVD. Therefore, the difference between groups at baseline will be the reason for the difference in disease progression. In order to deal with this problem, multiple regression analysis is applied and the baseline level will be included in multiple regression equation. Nevertheless, there is a potential bias related to the eligibility criteria. Only a subgroup of patients with AHI under 5 per hour will be included. Taking into account that the large proportion of cSVD patients has at least mild SOAS, the research will encompass only a small part of cSVD patients. However, we have to exclude even mild SOAS. Obstructive sleep apnea syndrome is accompanied by chronic sleep fragmentation as well as chronic hypoxemia that could worsen cognitive performance. Although the impact of mild SOAS on cognitive performance is still controversial (106–108), we cannot be sure that the presence of this condition will not influence the outcome. Taking into account that LMs in general and PLMS, in particular, could be associated with respiratory events, we would not include patients with even mild OSA with the purpose to avoid the presence of confounding factors.

Notwithstanding these limitations, the results of our study could elucidate the role of PLMS in cSVD progression and provide information about its possible influence on assessed outcomes—cognitive decline progression and MRI changes.

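### The regression sample sizes of 59 and 399 are complete-case numbers stated as enrolment numbers, with no allowance for two-year loss, and the term enrolled is used in two senses

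*Protocol article*

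**What the plan says.** Statistical Analysis and Sample Size Calculation sizes the key analysis with a rule for linear regression, "N = 392 + p for small, N = 52 + p for medium" effect size, and takes p as the covariate count: "there are seven independent variables (*p* = 7". The results are given as enrolment figures: "N = 52 + 7 = 59 participants should be enrolled" for a medium effect and "392 + 7 = 399 participants should be enrolled" for a small one. Recruitment is staged: "59 patients should be enrolled initially, and when no effect is revealed, the sample size should be enlarged up to 399". The same section then sizes a two-group comparison, described as interim, and arrives at a minimum of 98 patients. It does not say how that minimum relates to 59.

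Under Outcomes, the primary variable is the percentage change in total WMH volume from baseline. Protocol Outline schedules brain MRI at weeks 0 and 104. The consent text under Exclusion Criteria lets participants withdraw at any time.

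On when a patient counts as enrolled, the Abstract enrols subjects whose AHI is under 5, that is, after PSG. Protocol Outline says "All enrolled patients will undergo overnight PSG at baseline". The text under Exclusion Criteria adds "Patients with identified apnea/hypopnea index (AHI) equal to or more than 5 will be excluded", and Nocturnal PSG speaks of excluding such patients from the study.

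**The concern.** A sample-size formula returns the number of patients who contribute an outcome. Here a patient contributes only if the second MRI is obtained two years after the first. If 59 or 399 are enrolled and some do not return, the regression runs on fewer patients than the rule asks for.

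The first stage matters most, because the decision to go on to 399 depends on seeing no effect at 59. Lower power there makes it more likely that a real medium-sized effect is missed at that step.

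The unsettled meaning of enrolment adds to this. If the count starts before PSG, patients with AHI of 5 or more also come out of it, so a reader cannot tell which count has to reach 59 or 399.

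**Working it through.** **Inputs.** From Statistical Analysis and Sample Size Calculation: constants 52 and 392 (and 22 for a large effect), p = 7, and one tested PLMS parameter in addition. From Outcomes and Protocol Outline: the outcome needs MRI at weeks 0 and 104. Loss rate: not given, so 10% and 20% are assumed.

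**The plan's own figures.** 52 + 7 = 59 and 392 + 7 = 399. Both reproduce, and nothing is added for loss.

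**What the rule implies.** The article states no power for 59 or 399, so it has to be inferred from the constants. For one coefficient at two-sided 5% and 80% power, (1.960 + 0.842)² = 7.849. Dividing by f²:

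- 7.849 / 0.02 = 392.4 (small)
- 7.849 / 0.15 = 52.3 (medium)
- 7.849 / 0.35 = 22.4 (large)

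These match 392, 52 and 22. The rule therefore targets 80% power at two-sided 5% in complete cases, with f² = 0.02 for small and 0.15 for medium.

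**Power after loss.** Noncentral F with 1 numerator df, N − 9 denominator df (seven covariates plus the tested parameter) and noncentrality f² × N, where N is the number analysed, rounded down.

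| Assumed loss | N from 59 | Power, f² = 0.15 | N from 399 | Power, f² = 0.02 |
|---|---|---|---|---|
| 0% | 59 | 0.831 | 399 | 0.805 |
| 10% | 53 | 0.787 | 359 | 0.762 |
| 20% | 47 | 0.735 | 319 | 0.712 |

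A ninth predictor, the baseline value that the Discussion says will be included, changes these by less than 0.001.

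**Margin.** By the same method, 80% power needs 55 and 395 patients. So 59 can lose 4 (4/59 = 6.8%) and 399 can lose 4 (4/399 = 1.0%) before power falls below 80%.

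**Enrolment needed to keep the evaluable numbers**, N / (1 − loss), rounded up:

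- 10%: 59/0.9 → 66; 399/0.9 → 444
- 20%: 59/0.8 → 74; 399/0.8 → 499

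**If 98 are enrolled instead of 59.** At f² = 0.15, power is 0.967 with no loss (98), 0.948 at 10% (88), 0.921 at 20% (78) and 0.881 at 30% (68).

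**The case against.** The strongest reply is that the same section asks for at least 98 patients. If that governs, the medium-effect regression is safe: power is still about 0.88 at an assumed 30% loss. This stands, and it limits the result for 59 to the case where enrolment stops at 59. It does not help the 399, and the section never says which of 59 and 98 governs the first stage.

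It is also fair that every loss rate here is assumed, and that at 10% the drop is modest. That stands as a limit on size. It does not change the fact that complete-case numbers are labelled as enrolment numbers. Nor is this a detail left to an analysis plan, since the article itself fixes the enrolment figures.

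A reader might infer two stronger points, and the article supports neither.

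- **A much larger shortfall through PSG exclusions.** The Discussion does say that "the large proportion of cSVD patients has at least mild SOAS". But the Abstract enrols after the AHI result, and Protocol Outline can be read to agree, because patients who passed PSG have also undergone it. No exclusion rate is given. What remains is inconsistent wording.
- **Attrition defeats the power stated for the 98.** That calculation is the only one with a stated power (β = 0.2). Its comparison is called interim and has no time point, so if it is made at baseline, two-year loss does not touch it. It also misses 80% before any loss. At 49 per group, power is 0.69 two-sided or 0.79 one-sided if 0.5 is a standardised effect, and 0.52 or 0.64 if 0.5 is a raw difference with SD 1.22. That shortfall comes from its derivation and is a separate matter.

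**Conclusion.** The point holds for 59 and 399. They count patients with both scans but are presented as patients to enrol. The 80% power implied by the rule is lost once more than 4 patients drop out, about 7% of 59 or 1% of 399. At an assumed 10% to 20% loss, power is 0.79 to 0.73 at 59 enrolled and 0.76 to 0.71 at 399 enrolled.

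This rests on f² = 0.15 and 0.02 as recovered from the rule's constants, on assumed loss rates, on analysis of patients with both scans and, for the first figure, on enrolment stopping at 59. The shortfall is moderate. The two senses of enrolment are a wording inconsistency to reconcile, with no demonstrated numerical effect.

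**What to change.** 1. Restate 59 and 399 as patients with AHI under 5 and evaluable MRI at both week 0 and week 104. Alternatively, keep them as enrolment numbers and state the power retained at an assumed loss: 0.787 and 0.735 for 59, and 0.762 and 0.712 for 399, at 10% and 20%.
2. Say how 59 relates to the minimum of 98, and which number governs the first stage.
3. Use enrolment with one meaning, after PSG eligibility, in the Abstract, Protocol Outline, Nocturnal PSG and the sample-size section.

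Keeping the numbers and reporting retained power costs only wording and a slightly less favourable stated power. Restating them as evaluable patients means recruiting more if losses occur: for example 66 or 74 in place of 59, and 444 or 499 in place of 399, at 10% or 20% loss.

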PLMS is a condition characterized by periodic episodes of repetitive and stereotypic flexions of the hips, knees, and ankles (less common—arms movements) that manifests during the sleep. Diagnosis of periodic limb movements disorder (PLMD) requires conformity with two criteria. Firstly, periodic limb movements index (PLMI) >5/h in children and >15/h in adults must be detected by polysomnography (PSG). Second, PLMS in sleep must lead to clinically significant sleep disturbance or impairment in different relevant areas of functioning and cannot be better explained by another current sleep, medical, or neurological disorder such as narcolepsy, restless leg syndrome (RLS), or REM sleep behavior disorder (13, 14). The prevalence of PLMS worldwide, including the Russian population, is estimated to be 3.9–6% in the general population and around 34% in aged patients (above 60 years) (15, 16).

PLMS are described to be associated with various conditions, such as congestive heart failure (17), alcohol abuse (18), Tourette syndrome (19), syringomyelia (20), multisystem atrophy, and Parkinson's disease (21). Increased PLMS are also observed in a significant proportion of patients with various sleep disturbances (narcolepsy and obstructive sleep apnea). Moreover, this phenomenon is also detected in healthy subjects, and the prevalence increases with age (13, 16, 22). The closest association of PLMS is found with RLS. Approximately 85% of patients with RLS show high PLMI during nocturnal sleep (13, 22).

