### Hypothesis

PLMI equal to or more than 15 movements per 1 h of sleep is a predictor of small vessel disease progression.

Null hypothesis: the presence of PLMS with index ≥ 15/h has no influence on cSVD course.

Alternative hypothesis (one sided): the presence of PLMS with index ≥ 15/h worsens cSVD course.

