Movements with a duration equal to or more than 0.5 s are regarded as leg movements during the sleep (LMs), and those with a duration of <10 s are candidate LMs (68). Two to four unilateral candidate LMs from the two legs overlapping each other within 0.5-s interval are referred to as one bilateral candidate LM if the total duration is <15 s. The PLMS are defined as candidate LMs series of four or more, separated by more than 5 and <90 s and not interrupted by LM > 10 s (68, 69). The total number of LMs during the sleep will be divided by TST to obtain LMI. The PLMI will be calculated as the number of PLMS per hour of sleep (70). Periodic limb movements during wakefulness (PLMW) are movements that meet the criteria of PLMS but occur during bedtime when patient is awake. PLMAI is a number of associations of PLMS series with EEG arousals per hour of sleep (71). The number of PLMW per hour of wakefulness during bedtime is PLMW index. The number of intermovement intervals that will be 10–90 s long and all in sequences of at least three will be divided by the total number of intervals to calculate the PI (70, 72). This index lies within 0 (absence of periodicity) to 1 (complete periodicity). Total number of doublets of LMs with intermovement interval <10 s is divided by TST to gain SILMS index (73). Experimental and control groups will be formed based on PLMI. The experimental group will include patients with PLMI ≥ 15/h, and the control group will include subjects with PLMI <15/h.

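### The stated 49 per group does not give 80% power for the unpaired comparison: the plan's own inputs need 95 per group (two-sided) or 75 (one-sided), so 98 patients give about 52% or 64% power

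*Protocol article*

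**What the plan says.** All the inputs stand in one paragraph of the protocol article, Statistical Analysis and Sample Size Calculation. The regression calculation comes first (59 patients, enlarged to 399 if no effect is seen). The paragraph then adds a comparison of the two PLMI groups, planned as an interim analysis, by unpaired t-test or Mann–Whitney test. On that test it says: "will be applied, and it requires standard deviation (SD) to calculate the sample size". The inputs are an SD of 1.22 from the cited cross-sectional study, "given probability for rejecting the null hypothesis α = 0.05" and "probability of failing to reject the null hypothesis under the alternative hypothesis β = 0.2 and effect size = 0.5". The result is "effect size = 0.5, group size *N* = 49 is received when rounded up to the next highest integer", doubled to at least 98 patients, with the caveat that "this number could be changed after another value of SD will be received".

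The paragraph gives neither the sidedness of the test nor the scale of 0.5. The Hypothesis section does give a direction: "Alternative hypothesis (one sided): the presence of PLMS with index ≥ 15/h worsens cSVD course". The statistical section elsewhere sets only p < 0.05.

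On allocation, the Nocturnal PSG section says "Experimental and control groups will be formed based on PLMI", so group sizes are observed, not assigned. The Background section gives a PLMS prevalence of "around 34% in aged patients (above 60 years"). The section on pathophysiology and cardiovascular effects says that the prevalence among cSVD patients has not been evaluated.

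**The concern.** For two independent groups, the variance of the difference in means carries a contribution from each group. With a standardised difference of about 0.41, 80% power should need well over 49 per group. A size near 49 is what one expects when a single sample, or one set of paired differences, is tested.

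At stake is the power claimed for a planned comparison on the study's central question. If 98 patients are recruited in the belief that beta is 0.2, the real chance of missing a difference of 0.5 is much larger. The SD caveat does not cure this: a new SD put through the same calculation would again give about half the two-sided size needed.

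**Working it through.** **Inputs** (Statistical Analysis and Sample Size Calculation): SD 1.22; effect 0.5; alpha 0.05; power 0.80; unpaired t-test; 49 per group. Sidedness is not given there, so both are shown.

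**Scale of 0.5.** The text says that the SD is required and that N changes with it. That is true only if 0.5 is a raw difference. Then d = 0.5/1.22 = 0.4098 and d² = 0.1680.

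**Step 1: look for the plan's 49.** One-sample or paired t-test, two-sided:
- Normal formula: n = (1.960 + 0.842)²/d² = 7.849/0.1680 = 46.7.
- Exact noncentral t: 48.7, rounded up to 49. Power is 79.4% at n = 48 and 80.3% at n = 49.

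This matches 49 and uses every stated input, but it is not the test that is named.

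**Step 2: the test that is named.** Unpaired t-test, 1:1, n per group = 2(z_alpha + z_beta)²/d²:

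| | Normal formula | Exact t | Per group | Total |
|---|---|---|---|---|
| Two-sided | 2 × 7.849/0.1680 = 93.5 | 94.4 | 95 | 190 |
| One-sided | 2 × 6.183/0.1680 = 73.6 | 74.3 | 75 | 150 |

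Neither row gives 49. The Mann–Whitney test, at its efficiency of 0.955 under normality, needs slightly more: 94.4/0.955 = 98.9 two-sided and 74.3/0.955 = 77.8 one-sided.

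**Step 3: power with 98 patients.** The noncentrality is d × √(n1·n2/(n1 + n2)).
- 49/49: 0.4098 × √24.5 = 2.03 on 96 degrees of freedom. Power is 51.9% two-sided and 64.4% one-sided.
- 33/65 (98 × 0.34 = 33.3): 0.4098 × √21.9 = 1.92. Power is 47.5% two-sided and 60.2% one-sided.

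The second line assumes that the 34% background prevalence carries over to the enrolled patients. The protocol does not say so.

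**Step 4: difference detectable at 80% power with 98 patients, SD 1.22.**
- 49/49: 0.70 two-sided, 0.62 one-sided.
- 33/65, same assumption: 0.74 two-sided, 0.65 one-sided.

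**Step 5: the other reading, 0.5 as Cohen's d.** Unpaired, 1:1:
- Two-sided: 62.8 (normal) or 63.8 (t), so 63 or 64 per group.
- One-sided: 49.5 (normal) or 50.2 (t), so 50 or 51 per group. Power at 49/49 is 79.7% (normal) or 79.2% (t).

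**The case against.** The best defence is the last line of the working. The text says only effect size, and the declared alternative is one-sided. If 0.5 is Cohen's d and the test is one-sided, 49 per group has about 79% power, close to target. This reading still fails. Under the plan's own rule of rounding up it gives 50 or 51, not 49; it leaves the SD of 1.22 unused; and it contradicts the statement that the number changes with the SD. What stands is that the scale of 0.5 and the sidedness are both unstated and must be stated.

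Four stronger readings are tempting, and the documents do not support them.

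- **That power is simply 52%.** This needs a two-sided test, which the calculation does not state. Under the declared one-sided alternative it is 64%. Both figures belong in the statement.
- **That the split will be 34/66.** The 34% is a background figure for people above 60. The protocol says that prevalence in cSVD was not evaluated, and it excludes restless legs syndrome and AHI of 5 or more, conditions its Background links to increased PLMS. The split is unknown, so the 48% and 60% figures are a labelled sensitivity case.
- **That the authors demonstrably left out a factor of 2.** The match with the one-sample or paired size is exact after rounding, but the method is not shown. The shortfall does not depend on how it arose.
- **That a null result at 98 would be taken as adequately powered evidence of no difference.** The text does not say this. The 98 is a minimum for an interim comparison, beside a regression plan that moves towards 399 when no effect is seen. At 399 patients the power for 0.5 with SD 1.22 would exceed 97% two-sided even at 34/66.

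The interim label limits the consequence but does not make the number right. The enlargement is tied to the regression result, so it does not guarantee this comparison the size that it needs.

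**Conclusion.** The point holds as an arithmetic error in the two-group calculation. On the plan's own inputs the unpaired t-test needs 95 per group two-sided or 75 one-sided, not 49. With 49 and 49, beta is about 0.48 or 0.36, not 0.2.

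This rests on 0.5 being a raw difference, which the plan's dependence of N on the SD implies, and on equal groups. Unequal groups lower the power further, by an amount that cannot be fixed in advance from the documents. The error is confined to this interim comparison; the regression-based sizes of 59 and 399 do not use it.

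**What to change.** In Statistical Analysis and Sample Size Calculation, state whether the group comparison is one- or two-sided and that 0.5 is a raw difference on the scale of the SD of 1.22. Then do one of the following.

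1. Keep 98 for the interim comparison and report what it delivers at 1:1: about 52% power two-sided or 64% one-sided for a difference of 0.5, and 80% power only for a difference of about 0.70 or 0.62. Add that power is lower if the groups are unequal.
2. Keep 80% power for 0.5 and give the correct size: 95 per group (190) two-sided or 75 per group (150) one-sided at 1:1. Add an allowance for unequal groups, labelled as an assumption. At 34/66 the exact calculation gives totals of 210.2, so about 211, two-sided and 165.4, so about 166, one-sided.

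In either case, do not present 98 as the number that gives beta = 0.2, and use the unpaired formula if the size is revised with a new SD.

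The first option costs one corrected paragraph and a less favourable power statement, with no extra patients. The second adds 92 patients (190 − 98) or 52 (150 − 98) to this comparison at 1:1, still within the 399 that the regression plan already allows for.
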